**Methods:**

This is a single-center, block-randomized, two-arm parallel randomized controlled trial (RCT) will be conducted at the Brain Hospital Affiliated with Guangzhou Medical University, Guangdong, China. Sixty-six participants will be allocated to an intervention or control group via block randomization. Inclusion criteria are (1): diagnosis of MDD and NSSI per DSM-5 criteria; (2) aged 12–18 years; (3) provision of informed consent; and (4) adequate comprehension, communication, and writing abilities. Exclusion criteria include comorbid other mental disorders, history of serious physical illness, receipt of systematic horticultural therapy within the past three months, allergies, or suicidal risk behaviors.The control group will receive treatment as usual. The intervention group will receive TH in addition to treatment as usual for two weeks. The primary outcome is the severity of NSSI. Secondary outcomes include depression, alexithymia, self-efficacy, sleep quality, and loneliness. All outcomes will be assessed at baseline (T_0_) and immediately post-intervention (T_1_).

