### Study design

2.1

This is a single-center, block-randomized, two-arm parallel randomized controlled trial (RCT). The study protocol adheres to the SPIRIT 2025 statement (27). Participants are allocated in a 1:1 ratio to two groups via block randomization. The control group receives treatment as usual (TAU). The intervention group will receive Therapeutic Hrticulture (TH) in addition to TAU. The intervention period is two weeks. Assessments are conducted at baseline (T_0_) and immediately post-intervention (T_1_). The study flowchart is presented in **Figure 1**, and the schedule of enrollment, interventions, and assessments is detailed in **Table 1**.

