This study employs a blinded design. Due to the nature of TH intervention, blinding of participants and intervention facilitators is not technically feasible. However, outcome assessors and data analysts remain blinded to group allocation. To minimize the risk of unblinding due to environmental cues in the closed ward setting, the following measures will be implemented. Outcome assessments will be conducted in a designated room that is physically separate from the intervention area and not used for TH activities. Assessment sessions will be scheduled at times that do not overlap with TH sessions. Participants will be instructed not to disclose their group assignment or discuss TH activities during assessments. If accidental unblinding of an assessor occurs, this will be documented, and a different blinded assessor will complete the remaining assessments for that participant. Communication regarding group allocation between researchers and assessors is strictly prohibited. All assessment forms and study documents identify participants only by a study ID, with no group information included. Final unblinding will occur according to the pre-specified study protocol upon trial completion. Additionally, emergency envelopes containing participant allocation and treatment information are prepared in advance. In the event of a serious adverse event (SAE) where the treating physician must know the specific intervention to provide emergency medical care, and following confirmation by the principal investigator, the emergency unblinding procedure will be initiated immediately in accordance with the protocol, with detailed documentation of the event.

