#### Therapeutic horticulture

2.4.2

The intervention group will receive the TH intervention based on the healing system framework, in addition to the TAU received by the control group. Specifically, while receiving the identical two-week regimen of TAU as the control group, the intervention group participates in the additional TH program. The TH is delivered in a group format, with 3 to 6 participants per group. Sessions are conducted in the psychotherapy room of the psychiatric ward at the Affiliated Brain Hospital of Guangzhou Medical University. The intervention lasts for two weeks, comprising four sessions per week, each lasting 60 to 90 minutes. The TH protocol was developed by the research team under the guidance of domain experts, based on the healing system theoretical framework. The detailed intervention protocol is presented in **Table 2**.

**Table 2 T2:** Therapeutic Horticulture intervention program.

Session	Activity	Objective
1	1.1 Sensory Immersion & Ice-breaking	-Enhance interest, encourage self-expression, and promote social interaction.
	1.2 Craft Self-made Grass Head Dolls	-Enhance self-efficacy.
2	2.1 Divide & Plant Greenery	-Alleviate stress, enhance self-efficacy, and promote social interaction.
	2.2 Prepare Homemade Orange Peel Seasoning	-Regulate emotions and enhance self-awareness.
3	3.1 Create Simple Pressed Flowers	-Encourage acceptance of outcomes and recognize the growth potential of appropriate pressure.
	3.2 Creative Leaf Art & Printing	-Externalize emotions and reduce emotional repression.
4	4.1 Cooperative Flower Basket Assembly	-Promote social interaction and enhance self-efficacy.
	4.2 Sensory Discrimination of Flowers	-Relieve stress and facilitate emotional expression.
5	5.1 Herbal Tea Tasting	-Relax the body and mind, and focus on the present.
	5.2 Pot Painting & Decoration	-Promote non-verbal self-expression.
6	6.1 Cooperative Nutrient Soil Preparation	-Relieve stress and reduce social avoidance.
	6.2 Combination Potted Plant Arrangement	-Facilitate the expression of inner emotions.
7	7.1 Create Stamping & Embossing Cards	-Enhance self-efficacy, encourage self-expression, and promote social interaction.
	7.2 Craft Self-made Sachets	-Regulate emotions, enhance self-efficacy.
8	8.1 Plant Harvesting & Tea Preparation	-Enhance positive emotions and boost self-efficacy.
	8.2 Achievement Sharing & Reflection	-Strengthen self-efficacy and hope, reduce loneliness, and foster responsibility and connection.

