All plant materials used in this program are pre-selected by the research team based on the healing system framework to ensure consistency of sensory stimuli across activities. The plants include aromatic herbs such as mint, patchouli, and lavender; fresh flowers such as spray roses and sunflowers; foliage plants such as fittonia and miniature coconut palm; and edible plants such as citrus fruits and cherry tomatoes. All materials are screened for non-toxicity and potential allergens prior to use. The same core plant materials are used across all intervention groups to ensure standardization. To foster engagement and a sense of ownership, participants may choose from a limited set of options in certain activities, such as selecting preferred flowers for basket assembly or choosing among herbal tea varieties.

To ensure standardization and safety, the TH facilitators must complete standardized TH training through online courses, academic conferences, and practical workshops. They are permitted to deliver the intervention only after mastering the relevant theory, techniques, and practical skills, and upon passing a competency assessment. The principal investigator will assess and supervise adherence to the intervention protocol. All necessary materials are prepared prior to each session. Each session follows a standardized procedure to ensure safety and consistency. Sessions conclude with a summary and sharing segment, during which participants are encouraged to share their experiences and reflections, and the facilitator addresses any questions. Following the session, all materials are inventoried, recorded, and stored properly.

To enhance participant engagement and adherence, the facilitator provides each participant with an activity stamp card. After each TH session is completed, the facilitator seals the activity stamp card. Participants who collect all eight stamps receive a commemorative certificate and a small gift at the final session. Furthermore, the highlights of the next session are previewed verbally at the end of each meeting. The facilitator also provides a reminder for the upcoming session one day in advance.

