#### Primary outcome

2.5.1

The primary outcome is the change in the NSSI level score from baseline to post-intervention. The frequency and resulting harm of NSSI are assessed using the Adolescents Self-Harm Scale (ASHS), a 19-item self-report questionnaire (28). An ASHS total score greater than 0 indicates the presence of NSSI behavior. The NSSI level score is calculated by multiplying its frequency score by its harm score. A higher total score indicates greater NSSI severity (Cronbach’s α=0.93-0.97) (29).

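### A reward given only in the TH arm, at a closing session aimed at self-efficacy and loneliness, precedes the only outcome assessment, and the protocol sets no minimum gap between them

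*Protocol article*

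**What the plan says.** **Timing of outcomes.** Section 2.1 states: "Assessments are conducted at baseline (T_0_) and immediately post-intervention (T_1". The abstract and section 2.6 agree. No hour, day or window relative to session 8 is given. Table 1 puts T1 in a closeout column after Week 2, but the intervention row is marked in that column too.

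**Separation rule.** Section 2.3 requires only this: "Assessment sessions will be scheduled at times that do not overlap with TH sessions". It also requires a separate assessment room, blinded assessors, and participants told not to reveal their group. Participants themselves are not blinded.

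**Content of session 8.** In Table 2 the first activity has the objective "Enhance positive emotions and boost self-efficacy". The second, which covers sharing of achievements and reflection, has the objective "Strengthen self-efficacy and hope, reduce loneliness, and foster responsibility and connection".

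**Reward.** Section 2.4.2 gives its purpose: "To enhance participant engagement and adherence, the facilitator provides each participant with an activity stamp card". It then adds: "Participants who collect all eight stamps receive a commemorative certificate and a small gift at the final session".

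**Comparator and follow-up.** Controls receive TAU alone (section 2.4.1), with no closing event or gift described. The limitations in section 3 acknowledge that there is no follow-up, and treat this as a question of whether effects last.

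**Instruments.** NSSI frequency and harm "are assessed using the Adolescents Self-Harm Scale (ASHS), a 19-item self-report questionnaire" (section 2.5.1). GSES and UCLA-LS are two of the five secondary outcomes (section 2.5.2).

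**The concern.** The trial asks whether a two-week TH course, added to TAU, improves NSSI and psychosocial functioning. T1 has to carry that answer alone. If T1 falls within hours of session 8, GSES and UCLA-LS are completed just after an activity designed to move those two constructs, and some respondents have just received a gift. Nothing similar happens in the control arm.

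A response that fades by the next day would then be read as a result of the course. With no later measurement, the data cannot separate the two. The planned analysis does not help. Baseline adjustment cannot remove a shift that arises after baseline in one arm, the false discovery rate correction deals with multiplicity rather than bias, and assessor blinding does not protect a scale that an unblinded participant fills in.

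**Working it through.** **1. What the text fixes and what it leaves open**

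| Question | Answer in the protocol article | Place |
|---|---|---|
| Is the reward given before T1? | Yes. It is given at session 8, and T1 follows the intervention | 2.1, 2.4.2 |
| Is a same-day T1 ruled out? | No. Only overlap with a session is barred | 2.3 |
| Is a same-day T1 scheduled? | No. The timing is relative to the two-week intervention | 2.1, Table 1 |
| Who gets the reward? | TH participants with all eight stamps | 2.4.2 |
| Do controls have a matching event? | None described | 2.4.1 |
| Is there a later assessment? | No | 2.1, 3 |

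**2. Exposure by outcome**

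- GSES and UCLA-LS: most direct, because session 8 names self-efficacy and loneliness as targets.
- ASHS: less direct. It scores frequency multiplied by harm of self-injury, which is a report of behaviour. The plausible route is goodwill or under-reporting rather than a lift in mood.
- PSQI: asks about recent sleep, so a lift on one day should matter little.
- HAMD-17: described as a clinical instrument, and outcome assessors are blinded.

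**3. The plan's own figure (section 2.8)**

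Inputs: difference 13, SD 17.59, two-sided α = 0.05, power 80%, ratio 1:1, attrition 10%.

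n = 2 × (1.960 + 0.842)² × 17.59² / 13² = 28.74, rounded up to 29 per arm. Then 29 / 0.9 = 32.2, rounded up to 33 per arm, or 66 in total. The stated figures reproduce, and this point does not dispute them.

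Planned standardised effect: 13 / 17.59 = 0.739.

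**4. Illustration of size**

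The documents give no figure for a last-session shift. Let b be an assumed shift of the TH mean, in SD units, and suppose there is no true effect. With 29 per arm the standard error of the standardised difference is √(2/29) = 0.263. The two-sided rejection probability (normal approximation, one test at 5%, no baseline adjustment) is Φ(b/0.263 − 1.96) + Φ(−b/0.263 − 1.96).

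| Assumed shift b | On the ASHS scale (b × 17.59) | Share of planned effect (b / 0.739) | Rejection with no true effect |
|---|---|---|---|
| 0 | 0 | 0% | 5.0% |
| 0.1 SD | 1.8 points | 14% | 6.7% |
| 0.2 SD | 3.5 points | 27% | 11.9% |
| 0.3 SD | 5.3 points | 41% | 20.8% |

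Two qualifications apply. The last column is in SD units, so it can be read for GSES or UCLA-LS as well, but those two are also subject to the false discovery rate correction, which the calculation leaves out. And b is a mean over the whole arm. The gift reaches only those with all eight stamps, so if a share p receives it and their answers move by g, its contribution to b is p × g. Neither p nor g is given.

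**The case against.** The strongest reply is that a same-day T1 appears nowhere in the text, and that a journal article may leave the visit window to a fuller protocol. That is correct as far as it goes. A reader might infer from the word immediately that T1 follows session 8 on the same day, but the documents do not say so. What remains is what the article does fix: the reward comes before T1, and non-overlap is the only rule on separation.

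Second, the stamp card and gift belong to the TH package, and raising self-efficacy is intended content that also appears among the objectives of sessions 1, 2, 4 and 7. Every session closes with a sharing segment. A reader might take session 8 for a celebration, but Table 2 describes sharing and reflection. It is also true that a brief response to the last session is a real effect of TH. This stands in part. The difficulty is that the design cannot tell such a response from the effect of the course.

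Third, the gift is small, depends on attendance and not on scores, does not go to the whole arm, and is run by the facilitator while blinded assessors collect outcomes in another room. These safeguards limit the goodwill route, though they do not close it for unblinded participants completing self-report scales. General under-reporting by unblinded participants is a separate problem that would exist without any gift, and a one-day gap would not cure it.

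Fourth, the limitations already admit that there is no follow-up. They do so for persistence only, not for what the T1 contrast itself may contain.

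**Conclusion.** The point stands as a risk that the design leaves open and could easily avoid. The protocol permits the only outcome assessment to fall on the day of a TH-only closing session and reward, with no later measurement to show whether a response was short-lived. The likely direction favours TH. The exposure is mainly GSES and UCLA-LS, and only indirectly the primary ASHS score.

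The documents do not support the stronger statement that the self-report outcomes are biased, or that the primary result is compromised. That would need a scheduled same-day T1 and a known size of shift, and neither is given. The range of 0.1 to 0.3 SD is an assumption. It shows only that a modest one-arm shift would not be negligible beside a planned effect of 0.74 SD. The change is worth making because it costs little, not because harm has been shown.

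**What to change.** In section 2.4.2, state that the certificate and gift are handed over only after T1 is completed. The facilitator should do this away from the assessment room, so that assessors do not learn the allocation. If a participant declines T1, the gift should follow once the T1 slot has passed, so that it does not become an incentive to complete T1 in one arm only.

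In sections 2.1 and 2.3, state that no outcome scale is completed on a TH session day, that T1 takes place on the day after the last scheduled session, and that controls are assessed on the same study day. In both arms T1 should be booked before discharge.

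**Cost.** T1 and the gift move by about a day. The attendance incentive, sample size, analysis and number of assessments stay as they are. Participants are inpatients on one ward, so a one-day shift is practical, but T1 must be scheduled ahead of discharge or missing T1 data could rise. For the same reason a gap of two or three days is not advised.

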#### Treatment as usual

2.4.1

This study aims to evaluate whether adding TH to a standardized regimen of treatment as usual (TAU) provides additional benefit. To independently assess the additive effect of TH as an adjunctive therapy, the control group receives two weeks of TAU during the trial period. All TAU is provided according to the hospital’s standard clinical pathways. TAU comprises treatment and usual care. The treatment consists of antidepressant medication, supplemented by physical therapy, psychotherapy, and rehabilitation training. The usual care includes admission orientation, health education on symptoms, consequences and treatment options for depression and NSSI as well as the importance of treatment adherence, medication guidance, discharge planning, and psychological support.

During the study period, the provision of TAU is at the discretion of the attending physician. Participants are not restricted from receiving other treatments or care beyond the designated protocol. To address potential heterogeneity in TAU, the following TAU components will be systematically recorded for all participants throughout the trial: antidepressant medication, including drug name, daily dose, and any dose adjustments; physical therapy, including type, frequency, and duration; psychotherapy, including modality, number of sessions, and duration; and rehabilitation training, including type and frequency. If a participant’s symptoms worsen and require additional treatment, all related details are fully documented in the case report form. These data will be incorporated into the statistical analysis to control for potential confounding effects.

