Adherence to the TH intervention will be quantified as the proportion of scheduled sessions attended by each participant. Completion of at least six of the eight sessions, corresponding to 75% or more, will be considered adequate adherence. Overall adherence will be reported as the mean proportion of sessions attended across all participants in the intervention group, along with the number and percentage of participants meeting the adequate adherence criterion. An exploratory subgroup analysis will be conducted to examine whether the treatment effect on the primary outcome differs between participants with adequate adherence and those with inadequate adherence.

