### Statistical methods

2.9

Statistical analysis will be conducted by an independent statistician blinded to group allocation using SPSS 26.0 software. The analysis will adhere to the intention-to-treat (ITT) principle, employ two-sided tests, and consider a P-value of less than 0.05 as statistically significant.

The analysis of outcome measures will utilize three datasets: the full analysis set (FAS), the per-protocol set (PPS), and the safety set (SS). The FAS includes all randomized participants, analyzed according to their originally assigned groups. This is the primary dataset for efficacy analysis. All randomized participants are analyzed in the groups to which they were initially allocated. For missing data in the FAS, the primary outcome will be handled using multiple imputation to generate a complete dataset, upon which the primary analysis will be based. To assess the robustness of the results, a sensitivity analysis will be performed using the last observation carried forward (LOCF) method for imputation. The PPS includes participants with good adherence, who completed the full intervention, and had no major protocol deviations. This set will serve as another sensitivity analysis dataset to verify the stability of the primary analysis results. The SS includes all participants who received at least one dose of the intervention and is used for safety analyses. The evaluation of intervention effects for primary and secondary outcomes will primarily draw conclusions based on the analysis of the multiply-imputed FAS. The results from the LOCF-imputed FAS analysis and the PPS analysis will serve as sensitivity analyses to support the robustness of the conclusions. Safety indicators, such as the incidence of allergic reactions and adverse events, will be analyzed within the SS.

This study will conduct sensitivity analyses to evaluate the robustness of the results. These analyses will include repeating the primary analysis based on the FAS with missing data imputed using the LOCF method, as well as repeating the primary analysis on the PPS. If any baseline variables show imbalance (*P* < 0.1), they will be included as additional covariates in the model, followed by a corresponding sensitivity analysis.

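### The exploratory adherence subgroup analysis asks for a treatment effect that randomisation cannot identify, because adherence exists only in the TH arm and arises after allocation

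*Protocol article*

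**What the plan says.** Section 2.4.2 (Therapeutic horticulture) of the protocol article defines the measure: "Adherence to the TH intervention will be quantified as the proportion of scheduled sessions attended by each participant". It sets the cut-off: "Completion of at least six of the eight sessions, corresponding to 75% or more, will be considered adequate adherence". Overall adherence is to be reported as the "mean proportion of sessions attended across all participants in the intervention group", so it is a one-arm quantity. The same paragraph then plans an analysis, labelled exploratory, "to examine whether the treatment effect on the primary outcome differs between participants with adequate adherence and those with inadequate adherence".

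Section 2.4.1 describes the comparator: "the control group receives two weeks of TAU during the trial period". No TH sessions are scheduled for controls.

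Section 2.9 (Statistical methods) makes the full analysis set primary: "The FAS includes all randomized participants, analyzed according to their originally assigned groups". It also defines a per-protocol set: "The PPS includes participants with good adherence, who completed the full intervention, and had no major protocol deviations". Of its role it says: "This set will serve as another sensitivity analysis dataset to verify the stability of the primary analysis results".

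**The concern.** A treatment effect within a subgroup is a contrast between treated and control patients who belong to that subgroup. Here no control patient can be classed as adequately or inadequately adherent. The subgroups also form after randomisation, so membership can depend on prognosis, on motivation and on the course of the illness during the two weeks.

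The protocol itself supplies such a link. Section 2.2.3 allows discontinuation for clinical deterioration. Section 2.10 counts a clinically significant worsening of severe self-injurious behaviour as a serious adverse event that leads to withdrawal. A TH patient who worsens before the sixth session can therefore be classed as inadequately adherent because of the outcome. Section 2.6 seeks T1 data after early discontinuation of the intervention, so some of these patients may well be analysed.

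What is at stake is a reader taking a difference between the strata as evidence that more TH gives more benefit. The per-protocol set raises a related but weaker question, because it also selects on attendance and does not say how many sessions are required.

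**Working it through.** **Inputs from section 2.8.** Two-sided α = 0.05, power 80%, difference 13, SD 17.59, 33 per arm. The plan's own figure reproduces: n = 2 × (1.96 + 0.842)² × 17.59² / 13² = 28.74, so 29 per arm; 29 / 0.9 = 32.2, so 33 per arm and 66 in total. The 13 points and the SD serve as the yardstick below.

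**Identification.** Let G be the group and A adequate adherence. A is undefined in controls. If it is coded 0 there, then G × A = A for every patient, and two columns of the model matrix (intercept, G, A, G × A) are identical. With 33 per arm the rank is 3 of 4 at 70%, 80% and 90% adherence alike. The group-by-adherence term has no estimate. What remains is adherers against non-adherers within TH, or each TH stratum against all controls.

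**Illustration under no TH effect.** The documents give neither an adherence rate nor its relation to prognosis. Assume 80% adequate adherence and adherers 0.5 SD better, unadjusted:
- Gap: 0.5 × 17.59 = 8.8 points.
- Adherers minus all controls: −0.2 × 8.8 = −1.8.
- Non-adherers minus all controls: +0.8 × 8.8 = +7.0.
- Difference between the two: 8.8 points.

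**Range.** Let a latent tendency to attend have correlation ρ with a better T1 score, again with no TH effect (20,000 simulated trials per cell):

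| Adherent share | ρ | Adherers − controls | Non-adherers − controls | Spurious difference |
|---|---|---|---|---|
| 70% | 0.2 | −1.7 | +4.0 | 5.7 |
| 70% | 0.5 | −4.4 | +10.2 | 14.6 |
| 80% | 0.2 | −1.3 | +4.9 | 6.1 |
| 80% | 0.5 | −3.1 | +12.4 | 15.5 |
| 90% | 0.2 | −0.7 | +6.3 | 7.0 |
| 90% | 0.5 | −1.7 | +15.4 | 17.1 |

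At ρ = 0 all contrasts are zero to within simulation error.

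**Precision of the within-TH contrast.** The detectable difference at 80% power is 2.80 × 17.59 × √(1/a + 1/b), with a adherers and b non-adherers:
- 23 against 10: 18.7 points.
- 26 against 7: 21.0 points.
- 30 against 3: 29.8 points.

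**Per-protocol wording.** Section 2.9 gives no session count. With assumed independent attendance of 0.80 to 0.95 per session, all eight sessions are attended by 17% to 66% of TH patients (0.80⁸ = 0.168; 0.95⁸ = 0.663). At least six are attended by 80% to 99%. The reading chosen decides who is in the set.

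**The case against.** The strongest reply is that the analysis is labelled exploratory and nothing rests on it. Section 2.9 draws conclusions primarily from the multiply imputed full analysis set. That stands and limits the consequence, but the label does not supply the missing controls.

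The size of the artefact is also open to challenge. It depends on assumed adherence and prognosis, and it uses the raw SD. The planned ANCOVA adjusts for the T0 score and TAU covariates, which would remove whatever part of the gap they explain; the documents give no correlation from which to say how much. Nor would the artefact usually be significant. With 26 and 7 patients the standard error is 17.59 × √(1/26 + 1/7) = 7.5, so a gap of 8.8 gives z of about 1.2 and reaches two-sided P < 0.05 in about 22% of trials. A spurious adherence effect is therefore possible, not certain.

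Two stronger readings of the per-protocol set are tempting, and the documents support neither.
- A reader might infer that its contrast cannot be estimated either. It can: both arms contribute, and the condition on major deviations is not limited to TH. Only the session-attendance filter is one-armed. The matching bias is the adherers-minus-controls column, about −0.7 to −4.4 points, not the larger spurious difference. A supportive per-protocol analysis beside a primary intention-to-treat analysis is conventional.
- A reader might infer that sections 2.4.2 and 2.9 state contradictory thresholds. Section 2.9 states no number, and completing the intervention can mean eight of eight, the two-week course, or meeting the six-of-eight rule. The two definitions are unreconciled, not contradictory.

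**Conclusion.** The point holds for the subgroup analysis. As worded, it seeks a difference in treatment effect that this design cannot identify, and every runnable substitute is a non-randomised comparison. This follows from the definitions in sections 2.4.1 and 2.4.2 and needs no numerical assumption.

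The possible size does rest on assumptions. With no TH effect, the spurious difference is about 8.8 points for 80% adherence and a 0.5 SD gap. It is about 6 to 17 points for correlations of 0.2 to 0.5 and adherence of 70% to 90%. All of these are before baseline adjustment, against a design effect of 13.

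The primary analysis and the sample size are untouched. The per-protocol point is secondary: the adherence criterion needs defining, and agreement with the full analysis set is supportive, not confirmatory. The plan should be corrected here, but the trial's main conclusion does not depend on it.

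**What to change.** 1. In section 2.4.2, delete the adherence subgroup analysis as an analysis of treatment effect. Alternatively, keep it as a descriptive, non-randomised association between attendance and the T1 score within the TH arm, with no causal wording.
2. If a causal quantity related to adherence is wanted, estimate a complier-average causal effect by two-stage least squares. Include all randomised patients, use randomised group as instrument, and adjust for the T0 ASHS score. Sessions attended is the better exposure. A six-session cut-off treats patients with one to five sessions as unexposed, so any benefit they gain inflates the estimate. If the cut-off is used, say so. State the exclusion restriction and the wider interval. This estimates a different quantity and does not test whether the effect varies with adherence.
3. In section 2.9, give the per-protocol set an explicit session count and align it with the six-of-eight definition. State that the attendance filter applies to one arm only and that the result is supportive.

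The cost is a change of wording and, if item 2 is taken up, one small extra analysis. All the data are already to be collected, and the sample size does not change.
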